**Clinical grade of conjunctival hyperemia**

Clinical grade of conjunctival hyperemia occurred at the temporal bulbar conjunctiva was evaluated in each case. The clinical grade scores were 0 (none: no hyperemia of the bulbar conjunctiva), 1 (mild: the dilation of a few conjunctival blood vessels), 2 (moderate: the dilation of some conjunctival blood vessels), and 3 (severe: the dilation of many conjunctival blood vessels), based on Japanese guidelines for allergic conjunctival disease.6 Clinical grades were evaluated by 3 medical ophthalmic physicians, using the photographs taken at each of the 6 time points. We selected the most frequent grade value generated by the 3 physicians. When the scores differed among the 3 physicians, we selected the maximum value.

**Evaluating pixel coverage on conjunctival vessels using conjunctival hyperemia analysis software**

The photographs were processed using the software program developed by our group. Briefly, this software calculates the proportion of the blood vessels in the conjunctiva as the pixel percent coverage. The photographs were transferred to the software to calculate pixel coverage. To detect blood vessels, the green component of the RGB color model was used, and we adjusted the green value to accurately detect blood vessels within the region of interest (ROI). The pixel coverage was calculated by dividing the frequency of conjunctival blood vessel pixels by the total pixel frequency. For each selected region, the extent of hyperemia was determined by the percentage of pixelated blood vessels in the ROI. The ROI was depicted as the square, bordered by a blue line, with a vertical width of 60% and a horizontal width of 40%, using analysis software. The pixel coverage of conjunctival blood vessels was evaluated by 3 doctors using the ROIs within photographs taken at each of the 6 time points. We selected the most frequent pixel coverage value, as determined by 3 doctors. When the value differed among the 3 doctors, we selected the maximum value so as to not underestimate incidence of hyperemia.

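### Recording the most frequent of three pixel-coverage percentages, otherwise the maximum, mostly records the maximum unless values are coarsely rounded: a secondary endpoint is biased upward and loses precision

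*Protocol*

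**What the plan says.** The Protocol section on pixel coverage defines a ratio of pixel counts: "The pixel coverage was calculated by dividing the frequency of conjunctival blood vessel pixels by the total pixel frequency". The green-channel value is adjusted so that vessels are picked out, and the region of interest has set proportions. Three readers are used throughout, baseline included: "The pixel coverage of conjunctival blood vessels was evaluated by 3 doctors using the ROIs within photographs taken at each of the 6 time points".

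Their readings are combined in two steps. First, "We selected the most frequent pixel coverage value, as determined by 3 doctors". Then, "When the value differed among the 3 doctors, we selected the maximum value so as to not underestimate incidence of hyperemia".

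The section on the clinical grade (scale 0 to 3) has the same two steps: "We selected the most frequent grade value generated by the 3 physicians" and "When the scores differed among the 3 physicians, we selected the maximum value". It gives no reason for the second step.

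Under 'Study goals and objectives', the primary endpoint is median offset time judged on clinical grade, and pixel coverage is secondary. Under 'Statistical analyses', results are given as means with SDs. Secondary endpoints go to repeated-measures ANOVA and paired t-tests, and the relation of grade to coverage goes to a Jonckheere-Terpstra trend test. The number of decimals recorded and the variability between readers are not stated.

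**The concern.** A mode is a sensible summary for a few categories. For three readings of a near-continuous percentage it is seldom defined, so the fallback does most of the work. The maximum of three readings overstates the level and is less precise than their mean or median.

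The rule is also unstable, because a trivial difference between two readers decides whether the third reader's value is ignored or adopted.

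The stated reason does not rescue it. Coverage is a level, not an incidence. The rule also applies at all six time points, so it raises the baseline along with the post-instillation values.

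At stake are the reported mean coverage at each time and the precision of changes in coverage, which the protocol presents as the more objective measure of hyperemia.

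**Working it through.** The protocol gives no figure to reproduce; the target of 50 was set by feasibility.

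**Inputs.** From the protocol: 3 readers, 6 time points, mode first and maximum otherwise. Assumed: independent, unbiased, normal readings with between-reader SD *s* of 0.25 to 3 percentage points, recorded to *h* = 0.01, 0.1 or 1 point.

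**1. How often the maximum is taken.** The difference of two readings has variance 2s² and density 1/(2s√π) at zero. A given pair therefore coincides with probability of about h/(2s√π). With three pairs, P(any tie) ≈ 3h/(2s√π) = 0.846 h/s when h is small against s.

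- s = 0.25, h = 0.01: tie 0.034, all differ 96.6% (simulated 96.6%).
- s = 1, h = 0.1: tie 0.085, all differ 91.5% (simulated 91.7%).
- s = 3, h = 0.1: tie 0.028, all differ 97.2% (simulated 97.2%).

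Simulation of the full rule (400,000 draws) gives these ranges over s = 0.25 to 3: 97 to 99.7% at 0.01 point, 69 to 97% at 0.1 point, and 0.1 to 74% at whole percent.

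**2. Bias and precision when the maximum is taken** (exact order statistics for three normal readings):

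- E[max] = 3s/(2√π) = 0.846 s.
- Var[max] = s²(1 + √3/(2π) − 9/(4π)) = s²(1 + 0.276 − 0.716) = 0.56 s², so SD 0.748 s.
- Var[median] = s²(1 − √3/π) = 0.449 s², so SD 0.670 s.
- Var[mean] = s²/3 = 0.333 s², so SD 0.577 s.

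The variance ratio of maximum to mean is 0.56/0.333 = 1.7. In SD terms the maximum is 30% above the mean and 12% above the median, but 25% below a single reader.

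Simulated rule at s = 1 point:

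| Recorded to | All three differ | Bias | SD, rule | SD, mean | SD, median |
|---|---|---|---|---|---|
| 0.01 | 99.2% | 0.842 | 0.752 | 0.577 | 0.670 |
| 0.1 | 91.7% | 0.804 | 0.779 | 0.577 | 0.669 |
| 1 | 35.7% | 0.455 | 0.968 | 0.601 | 0.730 |

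**3. Instability.** Readings 10.0, 10.0, 14.0 are recorded as 10.0; readings 10.0, 10.1, 14.0 are recorded as 14.0. One reader moves by 0.1 and the result moves by 4. The mean goes from 34.0/3 = 11.33 to 34.1/3 = 11.37, and the median from 10.0 to 10.1. Whole-percent rounding does not remove this: 10, 10, 14 gives 10, and 10, 11, 14 gives 14.

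**4. Change from baseline.** If the maximum is taken at both times and post-instillation reader SD is k times the baseline value s, the bias in change is 0.846(k − 1)s. This is 0 for k = 1, 0.42 s for k = 1.5 and 0.85 s for k = 2. With k = 1 the error SD of a change is √2 × 0.748 s = 1.06 s for the maximum and √2 × 0.577 s = 0.82 s for the mean.

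**5. Clinical grade.** Here the maximum is a tie-break for three different grades. A simulation of 200,000 participants on an assumed grade time course compared the rule with the median of three:

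| Reader SD (grades) | Excluded from primary, rule vs median | Median offset (min), rule vs median | Mean offset capped at 240 min, rule vs median |
|---|---|---|---|
| 0.3 | 3.3% vs 3.2% | 120 vs 120 | 117.2 vs 117.1 |
| 0.5 | 6.5% vs 5.4% | 90 vs 90 | 119.7 vs 117.9 |
| 0.7 | 9.1% vs 7.4% | 90 vs 90 | 121.8 vs 117.6 |
| 1.0 | 12.8% vs 10.0% | 90 vs 90 | 122.9 vs 116.7 |

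Exclusions rise by 0.1 to 2.8 percentage points, and the median offset does not move.

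**The case against.** The strongest reply is that the size rests on inputs the protocol does not give. If coverage was rounded to whole percent and readers were close, the maximum was rarely taken. The software is called automated, and the text does not say that each doctor sets the green value separately; if the three results hardly depend on the reader, the rule hardly matters. This stands as a limit on size. The protocol does provide a rule for disagreement, however, so it expects some, and the instability remains at any precision.

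It is also true that the maximum of three, where it is consistently taken, varies less than a single reader, that a constant upward shift drops out of paired comparisons, and that a rank-based trend test ignores such a shift. The reported mean levels and the lost precision are untouched by these points.

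A reader might go further and infer that the primary endpoint is distorted, with an inflated baseline grade making hyperemia seem to resolve early. The documents do not support this. The primary endpoint uses grade alone, the tie-break acts at all six time points, and the modelled mean offset moved later by 0.1 to 6 minutes, with the median unchanged.

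A reader might also take the grade rule to turn 1, 1, 2 into 2. That would leave the preceding majority sentence without effect whenever physicians disagree; majority first, maximum only when all three differ, is the natural reading. The wording could be clearer, but this is not a contradiction.

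Nor should a high rate of three-way disagreement on grade be assumed. If each physician is right 70% of the time and one grade off 15% each way, all three differ in 6 × 0.7 × 0.15 × 0.15 = 9.5% of photographs, or at least once in six for 1 − 0.9055⁶ = 45% of participants. That requires a true grade of 1 or 2 in all six photographs, and it counts disagreements, not altered results.

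**Conclusion.** The point holds for pixel coverage. Unless values are coarsely rounded, the recorded figure is mostly the maximum of three readings. Mean levels are then about 0.85 reader SD too high, and rater variance is about 1.7 times that of the mean of the same data. These factors assume independent, unbiased, roughly normal readers; their size in percentage points depends on a reader SD that the protocol does not state. An inflated rise from baseline follows only if reader disagreement grows with hyperemia, which is possible but not documented. The rationale given for the rule does not justify it.

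For the clinical grade there is only a minor ambiguity and a slightly inferior tie-break. Overall this is a moderate improvement to a secondary endpoint in an exploratory trial, not a defect that endangers the primary result.

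**What to change.** In the pixel-coverage section, replace both combination sentences with one: for each photograph, at every time point including baseline, coverage is the mean (or median) of the three doctors' values. State the number of decimals recorded and report inter-reader agreement.

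In the clinical-grade section, use the median of the three grades. It equals the majority grade whenever two agree and the middle grade when all differ, so only the three-way disagreements change and the wording becomes unambiguous.

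The cost is about two sentences. The protocol already requires three readings per photograph, so nothing new is collected, provided the individual readings are kept. The one visible consequence is that reported coverage will be slightly lower.

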**IOP measurements using the iCare TA01i tonometer**

Our method for measuring IOP was selected in order to not affect conjunctival hyperemia. Although the “gold standard” evaluation method is the Goldmann applanation tonometer; however, use of anesthesia eye drops may affect hyperemia. Therefore, we selected a technique that did not require anesthesia and measured the IOP, in the sitting position, using an iCare TA01i tonometer.

**Statistical analyses**

The statistical analyses were performed using the statistical package R, version3.4.1 (R Foundation for statistical Computing, Vienna, Austria). For the primary endpoint, median offset of conjunctival hyperemia, we used a (two-tailed) 95% confidence interval, as follows. The lower bound was the [(n+1)/2−
[figure not shown]
]-th value counted from the minimum value. The upper bound was the [(n+1)/2−
[figure not shown]
]-th value counted from the maximum value. (The value [(n+1)/2−
[figure not shown]
] was the whole number part of (n+1)/2−
[figure not shown]
.) Participants with no increases in clinical grade post-instillation, relative to baseline, are excluded from the primary endpoint. Secondary endpoints were assessed by using repeated-measure analysis of variance (ANOVA) for all 50 participants. Paired-*t* test was carried out when it was judged that there was a significant difference between the two groups using ANOVA. The data were expressed as means ± SDs. *P* values *****< 0.05 and ****<** 0.01 were considered statistically significant. The correlation between the clinical grade and the value of pixel coverage of the blood vessels, and clinical grade and IOP, were subjected to statistical analyses using the Jonckheere-Terpstra Trend Test.

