# **Project summary**

The purpose of this study is to investigate the onset, offset, and kinetic changes of conjunctival hyperemia induced by 0.4% ripasudil ophthalmic solution; Glanatec ophthalmic solution in participants with open-angle glaucoma or ocular hypertension (OHT). Ripasudil-naïve adults (n=50) with glaucoma who were undergoing eye drop treatment are enrolled. Slit lamp photographs and IOP measures are performed in one eye at baseline and 10, 60, 90, 120, 180 min after instillation of ripasudil. The resultant photographic images are objectively evaluated by 3 ophthalmic physicians using conjunctival hyperemia-analyzing software. Dependent variables are conjunctival hyperemia offset, clinical changes, IOP, and pixel coverage of conjunctival vessels post-instillation. We determine correlations between clinical grade and pixel coverage, and clinical grade and IOP reduction. In this clinical study, it is possible to clarify the onset, offset and kinetic changes of conjunctival hyperemia, induced by 0.4% ripasudil ophthalmic solution, in patients with open-angle glaucoma or OHT.

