# **Study goals and objectives**

The primary endpoint of this study is to evaluate median offset time for conjunctival hyperemia induced by 0.4% ripasudil ophthalmic solution in patients with glaucoma. The evaluation is based on clinical grade scoring. The hyperemia offset time was determined as the time-point when clinical grade score increased by instillation of ripasudil returned to the baseline score. Additionally, the relationships among clinical grade changes over time, IOP, and pixel coverage on conjunctival blood vessels within 180 min post-instillation will also be evaluated for the secondary endpoints. The correlations between clinical grade and pixel coverage, and clinical grade and IOP reduction will be statistically analyzed. Furthermore, by using conjunctival hyperemia analyzing software, evaluation of conjunctival hyperemia will be more objective.

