# **Study Design**

**Study design:** Multicenter, prospective, interventional, non-randomized open-label study.

**Trial characteristic:** Exploratory

**Purpose of intervention:** Treatment

**Type of intervention: Medicine:** At the beginning of trial, one drop of 0.4% ripasudil solution will be instilled to the subjective eye.

**Target sample size:** 50

This clinical trial was not based on a statistical hypothesis test, and 50 cases were taken as the target number of cases from the feasibility of this trial.

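### The correlations of clinical grade with pixel coverage and with IOP reduction are objectives, but the only method fixed for them is a trend test, with no coefficient or confidence interval

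*Protocol*

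**What the plan says.** The Project summary states the aim: "We determine correlations between clinical grade and pixel coverage, and clinical grade and IOP reduction". Study goals and objectives repeats it: "The correlations between clinical grade and pixel coverage, and clinical grade and IOP reduction will be statistically analyzed".

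The method is in Statistical analyses, where one sentence covers both associations. It opens with "The correlation between the clinical grade and the value of pixel coverage of the blood vessels". The remainder of that sentence brings in the second pair and names the method for both: "and clinical grade and IOP, were subjected to statistical analyses using the Jonckheere-Terpstra Trend Test". Results below 0.05 and 0.01 "were considered statistically significant". No coefficient, slope or interval for either association appears anywhere in the protocol. The same section does give an order-statistic confidence interval for the primary endpoint, the median offset time.

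Three other statements matter. On sample size, Study Design says "50 cases were taken as the target number of cases from the feasibility of this trial", and it calls the trial exploratory and not based on a hypothesis test. One eye per participant is studied. The graders score that eye "using the photographs taken at each of the 6 time points", so each eye contributes up to six pairs of grade and pixel coverage.

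**The concern.** A correlation objective asks how closely two things move together. The method fixed for it answers a narrower question: is there evidence against no monotone trend?

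For grade and pixel coverage that question has little content. Both describe the conjunctival vessels in the same temporal photographs, so independence is implausible beforehand. Rejecting it says little about how well the software tracks the clinical grade. For grade and IOP reduction a trend is an open question, so the test does inform, but it still leaves the size of the relationship unstated.

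The risk is that a small p-value is read as a good correlation. Two further points compound it. The variable changes from IOP reduction in the objectives to IOP in the analysis, which are different quantities: IOP carries each eye's baseline level, and reduction does not. And the plan does not say whether the test uses one value per eye or all time points.

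**Working it through.** The protocol gives no effect size, power or correlation figure, so there is none to reproduce.

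**Inputs from the protocol.** 50 participants, one eye each; six time points; four ordered grades (0 to 3); marks at 0.05 and 0.01.

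**Assumptions, not in the protocol.** Two-sided test. Grade distribution either 20/40/30/10% or 25% in each grade. Latent correlation varied over a range.

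**1. What the test measures.** Jonckheere-Terpstra is equivalent to the test of Kendall's tau. In one simulated set of 300 pairs both gave z = 4.60 and p = 4.2e-6. The estimate behind that p-value was modest: tau-b 0.20, concordance 0.62. An effect size therefore follows from the same calculation, but the protocol does not ask for it.

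**2. Smallest significant association, one value per eye, no-ties approximation.**
- SE of tau under the null = sqrt(2(2n+5)/(9n(n−1))) = sqrt(210/22050) = 0.0976 for n = 50.
- p<0.05: tau = 1.960 × 0.0976 = 0.191. With r = sin(π·tau/2), r = 0.296 and r² = 0.088.
- p<0.01: tau = 2.576 × 0.0976 = 0.251, r = 0.385, r² = 0.148.

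**3. Moderate against strong, same approximation.**
- r = 0.5: tau = (2/π)·asin(0.5) = 0.333, z = 0.333/0.0976 = 3.42, p = 0.0006.
- r = 0.8: tau = 0.590, z = 6.05, p = 1.5e-9.

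Both fall below 0.01.

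**4. Simulation with four tied grades: chance of p<0.01.** The range covers the two grade distributions.

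| Latent correlation | 50 pairs, one per eye | 300 pairs, treated as independent |
|---|---|---|
| 0.2 | 8–10% | 72–76% |
| 0.3 | 26% | 98–99% |
| 0.5 | 77–78% | 100% |
| 0.7 | 99–100% | 100% |

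At 0.8 with 50 pairs (20/40/30/10% only) it was 100%. At 0.1 with 300 pairs it was only 14–17%, so pooling does not flag everything.

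The 300 column is 50 × 6 and was drawn as independent pairs, so it shows only the effect of the larger nominal count. In real pooled data six pairs share an eye, so the test's null variance does not apply and its p-value is not valid.

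**5. What an estimate would add.** Approximate 95% CI for a rank correlation at n = 50: tanh(atanh(r) ± 1.96·sqrt((1 + r²/2)/47)).
- 0.3: 0.02 to 0.54.
- 0.5: atanh = 0.549, half-width 1.96·sqrt(1.125/47) = 0.303, giving 0.24 to 0.69.
- 0.8: atanh = 1.099, half-width 1.96·sqrt(1.32/47) = 0.328, giving 0.65 to 0.89.

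The last two would carry the same mark under the plan, yet they support quite different statements about the software.

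**The case against.** **The choice of test is defensible.** This stands. A rank-based trend test suits a four-level ordinal grade against a continuous measure. It yields a signed statistic equivalent to Kendall's S, and its alternative is a monotone ordering. A reader might infer that the test can return nothing but a p-value against any trend at all; that is not so. The gap is that no effect size is asked for.

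**The SAP may add a coefficient.** It may, so it cannot be said that the correlations will never be estimated. But the protocol does not leave the method open. It names one, and that one does not by itself deliver the objective. It specifies an interval for the primary endpoint and none here.

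**The objectives set no target for strength, and the trial is exploratory.** True, but a trial that disclaims hypothesis testing is poorly served by a test alone.

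**Weak and strong links would not look alike.** At one value per eye this stands: correlations of 0.2 to 0.3 reach p<0.01 in 8–26% of trials, against 99–100% at 0.7. The stronger statement would need pooling, which the protocol neither states nor rules out.

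**The time-course summaries.** A reader might extend the criticism to "The data were expressed as means ± SDs". The protocol does not support that. The same eyes are measured at every time point, so with complete data the difference between two time-point means is the mean within-eye change. Repeated-measures ANOVA and paired t-tests are also planned.

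**Conclusion.** The concern holds as a mismatch between objective and method. The protocol sets two correlations as objectives and fixes for them a test of monotone trend, with no coefficient or interval and with IOP in place of IOP reduction.

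At one value per eye, significance begins at a tau of about 0.19 (roughly 9% of variance), and correlations from 0.5 to 0.8 usually receive the same P<0.01 mark. If all time points are pooled, correlations of 0.2 to 0.3 would usually be flagged too, and the p-value would be invalid.

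The tau thresholds rest on a no-ties approximation and a two-sided test. The percentages rest on assumed grade distributions. The mismatch itself needs none of these assumptions. It affects secondary endpoints only and should be corrected because doing so costs almost nothing.

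**What to change.** Revise the last sentence of Statistical analyses so that, for both associations, the stated result is an estimate with a 95% CI:

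- **Pixel coverage:** a within-eye or rank correlation (Kendall tau-b) with clinical grade, and the change in coverage per one-step change in grade.
- **IOP:** the same two quantities, using IOP reduction from baseline as in the objectives.
- **Intervals:** resample whole eyes, so that the six measurements of an eye stay together.
- **Unit:** state whether one value per eye or all time points enter. For IOP reduction, also state which grade is paired with which reduction: the protocol's own background reports that in healthy participants redness peaked at 5–15 min, while IOP fell between 30 min and 2 h.
- **Test:** keep Jonckheere-Terpstra as an accessory, on one value per eye.

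The cost is one paragraph and a little analysis work in R, which the protocol already names. No new data, visits or participants are needed.

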# **Safety Considerations**

The study conformed to Declaration of Helsinki standards. Potential participants for the clinical trial were provided with comprehensive information regarding the study protocol. This study was a trial with marketed product; phase 4 and an investigator- initiated clinical trial.

